#### Cryosurgery

In the control-group, one single freeze–thaw cryosurgery is conducted at visit 1, using an open spraying procedure with liquid nitrogen for each AK lesion. After formation of an ice ball, freeze time starts that should be between 5 and 10 s per lesion. At visits 2 to 6, the efficacy of the treatment is evaluated by the investigator. Cryosurgery will also be conducted at visits 2 to 5 in the case of non-cleared or newly developed AK lesions.

### Outcome assessment

The primary outcome parameter is the cumulative number of AK lesions observed between visits 2 and 6.

Secondary outcome parameters are complete clearance of AK on patient and lesion basis, new AK lesions since the last visit, cosmetic results as evaluated on assessment scales, patient-reported pain (visual analogue scale, VAS), local reactions, patient satisfaction score with cosmetic results, physician satisfaction score with cosmetic results, and patient-reported quality of life (Dermatology Life Quality Index, DLQI).

In addition, safety parameters are documented (adverse events and serious adverse events, AE and SAE).

Complete clearance is documented if a lesion is no longer visible and also imperceptible to the touch [17]. Photodamage variables to be evaluated are fine lines, mottled pigmentation, skin color, tactile roughness, sallowness, teleangiectasias, deep wrinkles, facial erythema, sebaceous gland hyperplasia, and global score for photoaging. Each photodamage variable is recorded on a 5-point scale (0–4, higher points indicating higher damage, modified after Dover and Zane) [15, 16].

Patient and physician satisfaction with esthetic outcome is assessed at visit 2 to 6. Patients and physicians can choose from very satisfied, satisfied, moderately satisfied, and not satisfied.

### Statistical considerations

#### Study hypothesis

The study objective can be formulated as a test of the null hypothesis H0: μ1 = μ0 versus the alternative hypothesis H1: μ1 ≠ μ0, where μ1 and μ0 represent the mean cumulative number of AKs in the MAL/daylight-PDT and cryosurgery group.

#### Sample size

Sample size calculation is based on the primary endpoint, that is the cumulative number of AK lesions. According to clinical experience, we expect a mean cumulative number of 10 AK lesions in the daylight-PDT group versus 14 lesions in the cryosurgery group with a standard deviation of 5 in both groups. To detect a difference of 4 with a standard deviation of 5 with a power of 1 − β = 80% at a two-sided alpha significance level of 0.05, the required sample size is 26 patients per group (a total of 52 patients to be analyzed). With a lost-to-follow-up rate of 10%, 29 patients per group (a total of 58 patients) are required.

#### Populations to be analyzed

The intention-to-treat (ITT) analysis set consists of all patients entering the study (i.e. all patients who are randomized and receive a patient identification number) and receiving at least one treatment. According to the ITT principle, all patients are analyzed as belonging to their randomized treatment, regardless of whether treatment is refused or discontinued, or whether other protocol deviations are known.

The per protocol (PP) analysis set consists of the ITT analysis set with no major protocol violations. Major and minor protocol deviations will be identified by medically trained staff before database lock.

The safety population consists of all patients receiving at least one treatment and who undergo at least one post-baseline safety assessment. The statement that a patient had no adverse events also constitutes a safety assessment.

#### Statistical analysis

The cumulative number of AK lesions (sum of all AK lesions from visit 2 to visit 6) is defined as the primary endpoint. A point estimate is presented as mean and standard deviation accompanied by the corresponding 95% confidence interval. Furthermore, the primary endpoint is compared between the MAL/daylight-PDT and the cryosurgery group by means of an analysis of covariance (ANCOVA) with treatment (MAL/daylight-PDT and cryosurgery) as fixed factor and initial AK at baseline and center as covariates. The results are presented in terms of least-squares means and associated 95% confidence intervals. All efficacy analyses are carried out on the intention-to-treat (ITT) population and will be two-sided at the significance level of 0.05.

All secondary endpoints are analyzed in a purely exploratory manner and are summarized by means of descriptive statistics. Thus, *p*-values and corresponding confidence intervals are only descriptive in nature. Safety variables are analyzed descriptively. Adverse events are presented in frequency tables. In addition, adverse events are tabulated by severity and relationship to study treatment.

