**Methods/design:**

In this multicenter, prospective, randomized, controlled, two-armed, observer-blinded trial, patients with a minimum of 5 mild-to-moderate AK lesions on photodamaged facial skin are randomly allocated to two treatment groups: DL-PDT with methyl aminolevulinate (MAL) and cryosurgery. In the DL-PDT group (experimental group), 5 treatments of the entire face are conducted over the course of 18 months. After preparation of the lesion and within 30 min after MAL application, patients expose themselves to daylight for 2 h. In the control group, lesion-directed cryosurgery is conducted at the first visit and, in the case of uncleared or new AK lesions, also at visits 2 to 5. The efficacy of the treatment is evaluated at visits 2 to 6 by documenting all existing and new AK lesions in the face. Cosmetic results and improvement of photoaging parameters are evaluated by means of a modified Dover scale.

Primary outcome parameter is the cumulative number of AK lesions observed between visits 2 and 6.

Secondary outcome parameters are complete clearance of AK, new AK lesions since the previous visit, cosmetic results independently evaluated by both patient and physician, patient-reported pain (visual analogue scale), patient and physician satisfaction scores with cosmetic results, and patient-reported quality of life (Dermatology Life Quality Index). Safety parameters are also documented (adverse events and serious adverse events).

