## Background

Actinic keratosis (AK) is one of the most frequently diagnosed skin diseases in dermatological practice. Clinical examination of the study participants of the Rotterdam cohort study aged >45 years showed a prevalence of up to 49% in men and 28% in women [1, 2]. Therefore, treatment of AK causes high costs for health insurances [3]. Consequent treatment of AK is necessary because of the possibility of malignant transformation. AK lesions are regarded as in situ squamous cell carcinomas [4] that progress to invasive squamous cell carcinomas in up to 20% of patients [5–7]. In 2015, ‘multiple actinic keratoses’ defined as more than 5 AK lesions per year or field cancerization of >4 cm^2^ have been acknowledged as a new occupational disease in Germany [8]. National and international guidelines recommend the treatment of AK upon diagnosis to prevent further progression into squamous cell carcinoma [9].

Besides several other treatment options, photodynamic therapy (PDT) with red light for illumination is characterized by high efficacy and good esthetic results, largely independent of patient adherence. Daylight-PDT (DL-PDT) is a new treatment approach that uses natural sunlight for illumination. DL-PDT is associated with less discomfort and pain compared to standard treatment protocols, and its efficacy in treating AK seems to be equal to that of conventional PDT with red light [10–12].

However, clinical trials investigating the efficacy of field-directed, repetitive DL-PDT for the prophylaxis of AK are lacking [11, 13, 14] as well as knowledge about the esthetic and rejuvenating effects of repetitive DL-PDT.

Therefore, the present study investigates the prophylactic effect of repetitive DL-PDT on the occurrence of AK as compared to lesion-directed cryosurgery. In addition, the rejuvenating effects of DL-PDT with regard to the clinical signs of photoaged skin are evaluated.

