### Study treatment

At every visit, the location of each AK lesion is documented within a chart and additionally marked on plastic sheets. The plastic sheets are marked with reference points of the face of each study participant, ensuring that the lesions will be found again at the next visit. Photo-documentation is carried out in a standardized manner at each visit.

Photodamage variables to be evaluated are fine lines, mottled pigmentation, skin color, tactile roughness, sallowness, teleangiectasias, deep wrinkles, facial erythema, sebaceous gland hyperplasia, and the global score for photoaging. Each photodamage variable is recorded on a 5-point scale (0–4, higher points indicating higher damage, modified after a scale from Dover et al. and Zane et al.) (Table 1) [15, 16].

**Table 1 Tab1:** Photodamage Score

Score	0	1	2	3	4
Global score for photoaging	facial skin smooth to the touch, no significant fine lines, uneven pigmentation, deep wrinkles, erythema, teleangiectasias, sebaceous gland hyperplasia on the cheeks, forehead, or in the perioral area	one area (cheeks, forehead, or perioral area) of significant roughness, deep wrinkles, erythema, teleangiectasias, sebaceous gland hyperplasia, dyspigmentation or fine lines	two areas of significant roughness, deep wrinkles, erythema, teleangiectasias, sebaceous gland hyperplasia, dyspigmentation or fine lines or one area of significant roughness, deep wrinkles, erythema, teleangiectasias, sebaceous gland hyperplasia, dyspigmentation and fine lines	three areas of significant roughness, deep wrinkles, erythema, teleangiectasias, sebaceous gland hyperplasia, dyspigmentation or fine lines or one area of significant roughness, deep wrinkles, erythema, teleangiectasias, sebaceous gland hyperplasia, dyspigmentation and fine lines	facial skin with photodamage higher than grade 3
Fine lines	none	very few, widely disseminated lines	some discreet lines	a moderate number of lines, in close proximity	many lines, in close proximity
Mottled pigmentation	evenly pigmented skin	minor hypo-pigmentation or hyper-pigmentation	small areas of very light hypo-pigmentation or hyper-pigmentation or moderately sized areas of light hypo-pigmentation or hyper-pigmentation	moderate hypo-pigmentation or hyper-pigmentation or small areas of pronounced hypo- pigmentation or hyper-pigmentation	major hypo- pigmentation or hyper-pigmentation

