Chronically sun-damaged skin is also characterized by sallowness, teleangiectasias, hyperpigmentations, roughness, and wrinkles. Therefore, simultaneous treatment of AK and photodamage is highly desirable. Several studies have reported on the rejuvenating effects of PDT [22–24], such as reduced fine wrinkles, mottled hyperpigmentation, tactile roughness, skin texture, teleangiectasias, facial erythema, and sallowness [25]. Only coarse wrinkles and sebaceous gland hyperplasia were not significantly improved. The cosmetic effects of topical PDT are supported by immunohistochemical analysis that showed both upregulation of collagen production and increased epidermal proliferation [26, 27]. Several studies have also shown a reduction in elastotic material in the dermis [28, 29]. These molecular effects together with the disappearance of Tp53, a marker for epidermal carcinogenesis, may explain why PDT is able to reverse the signs of photoaging [30].

Based on the findings after conventional PDT, the innovative research issue addressed in the present study is to investigate the prophylactic effect of repetitive PDT on the development of AK. As a secondary study endpoint, the rejuvenating effects of repetitive DL-PDT will be examined for the first time.

The reference therapy used in this clinical trial is cryosurgery − a frequently used treatment modality for AK that is recommended as a standard therapy in national and international guidelines and was used in most studies as standard therapy comparator for PDT. Complete remission rates are between 67 and 97% [31, 32]. Our aim is to compare a lesion directed standard therapy (cryotherapy) with a field directed therapy (DL-PDT) with respect to an expected prophylactic effect of a repetitive field directed PDT.

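### The primary endpoint measures total lesion burden, so on its own it cannot support the prophylaxis conclusion, and the only endpoint that isolates new lesions is exploratory.

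*Protocol article*

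**What the plan says.** The Statistical analysis section fixes the endpoint: "The cumulative number of AK lesions (sum of all AK lesions from visit 2 to visit 6) is defined as the primary endpoint". The abstract (Methods/design) says what enters each count: "The efficacy of the treatment is evaluated at visits 2 to 6 by documenting all existing and new AK lesions in the face".

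On the aim, the Background says "the present study investigates the prophylactic effect of repetitive DL-PDT on the occurrence of AK", compared with lesion-directed cryosurgery. The abstract's Discussion paragraph and the main Discussion also put prevention forward as the question. The title, the abstract's Background and the closing paragraph of the Discussion are broader and name treatment and prevention together.

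New AK lesions since the last visit is listed under Outcome assessment as a secondary parameter. Of that whole class the Statistical analysis section says: "All secondary endpoints are analyzed in a purely exploratory manner".

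The Sample size section states, from clinical experience, that "we expect a mean cumulative number of 10 AK lesions in the daylight-PDT group versus 14 lesions in the cryosurgery group". The SD is taken as 5 in each arm. The section does not split these means into residual and new lesions.

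**The concern.** A sum of visit counts has two sources: lesions that treatment failed to clear, and lesions that appeared afterwards. A baseline lesion that never clears can add up to 5; a lesion that first appears at visit 6 adds 1. Two arms with identical new-lesion rates can therefore differ on the primary endpoint simply because one treatment clears better.

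The risk lies in the conclusion. A significant primary result could be reported as a prophylactic effect when the arms differ only in clearance. Conversely, if cryosurgery clears better, the sum could shrink or hide a real preventive effect. The endpoint that would settle the matter has no confirmatory status.

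**Working it through.** **1. The plan's own figure.** With a difference of 4, SD 5, two-sided alpha 0.05 and 80% power, the t-based power is 0.791 at 25 per group and 0.807 at 26, so 26 per group is right. Allowing for 10% loss, 26 / 0.9 = 28.9, so 29 per group. The sample size reproduces.

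**2. Inputs.**
- DL-PDT clearance 89%: Discussion, complete remission at week 12 in a cited phase III study.
- Cryosurgery clearance: Discussion, "Complete remission rates are between 67 and 97"%. The midpoint is (67 + 97) / 2 = 82%.
- Five counts, visits 2 to 6; treatment at visits 1 to 5 (cryosurgery at visits 2 to 5 if lesions are present).
- Baseline count B: only the entry minimum of 5 is given. Assumed about 5, or 10.
- New lesions per interval, λ: not given. Assumed 1.7 or 1.5, and **equal in both arms**, that is, no preventive effect.
- Assumed: the cited rates apply per lesion and per session, and stay constant.

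**3. Formula.** Count at a visit = previous count × (1 − c) + λ. With A(c) = (1−c) + (1−c)² + … + (1−c)⁵, the expected sum over five visits is

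B × A(c) + λ × (5 − A(c)) / c.

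| c | A(c) | (5 − A(c)) / c |
|---|---|---|
| 0.67 | 0.491 | 6.730 |
| 0.75 | 0.333 | 6.223 |
| 0.82 | 0.219 | 5.830 |
| 0.89 | 0.124 | 5.479 |
| 0.97 | 0.031 | 5.123 |

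**4. Can the planned 10 versus 14 arise with no prevention?** Solve 0.124B + 5.479λ = 10 and 0.491B + 6.730λ = 14 with the same λ. The solution is B = 5.07, λ = 1.71. Each arm then has 5 × 1.71 = 8.55 new lesions. The remainder, residual and repeat counts, is 10 − 8.55 = 1.45 with DL-PDT and 14 − 8.55 = 5.45 with cryosurgery. The whole difference of 4 is clearance. B and λ were solved to hit the two targets, so this shows possibility, not likelihood.

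**5. Range over the cited cryosurgery rates.** Difference is cryosurgery minus DL-PDT; DL-PDT sums are 10.0 and 9.45.

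| Cryosurgery clearance | B = 5.07, λ = 1.71 | B = 10, λ = 1.5 | Power at 26 per group, SD 5 |
|---|---|---|---|
| 67% | 14.0 (+4.0) | 15.0 (+5.5) | 81% to 97% |
| 75% | 12.3 (+2.3) | 12.7 (+3.2) | 38% to 62% |
| 82% | 11.1 (+1.1) | 10.9 (+1.5) | 12% to 18% |
| 89% | 10.0 (0) | 9.45 (0) | 5% |
| 97% | 8.9 (−1.1) | 8.0 (−1.5) | 12% to 18% |

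**6. Unequal intervals.** The visits are 3, 3, 6, 6 and 6 months apart. Making new lesions proportional to time, with λ set so that the DL-PDT sum is 10, gives +3.8 at 67% and −1.0 at 97% for B = 5, and +5.5 and −1.5 for B = 10. The pattern is unchanged.

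**The case against.** The strongest reply is that the aim is joint. The title and the close of the Discussion name treatment and prevention, and the Study hypothesis section states the objective as a comparison of mean cumulative AK numbers. For that aim, total burden is a proper primary endpoint. This stands. A reader might infer that the trial has no confirmatory test of its own question; the document does not support that. Only the prophylaxis part lacks one.

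Second, the exact match to 10 versus 14 uses the lowest cited cryosurgery rate and fitted inputs. The document does not say whether the 67 to 97% range is per lesion or per patient, and a mean baseline at the entry minimum is unlikely. This also stands. A reader might infer that clearance probably explains the planned difference; at the 82% midpoint it explains only 1.1 to 1.5 of 4, roughly a quarter to just over a third.

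Third, persistence does not dominate the total. In the fitted case new lesions make up 8.55 / 10 = 86% of the DL-PDT sum and 8.55 / 14 = 61% of the cryosurgery sum, and a lesion counted five times is rare (0.33⁵ = 0.4% at 67% clearance). That limits the size of the problem but does not remove it.

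Fourth, new lesions and lesion-level clearance are already secondary endpoints, so a reader could see the components. True, but descriptively only. The ANCOVA's adjustment for baseline count does not help here: it corrects for the starting number, not for different clearance after randomisation.

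Finally, Outcome assessment speaks of lesions observed between visits 2 and 6, which could mean distinct lesions. The Statistical analysis section defines a sum, and even a distinct count would include uncleared baseline lesions.

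**Conclusion.** The point holds in limited form, as something that should be fixed. The primary endpoint suits the joint aim and its analysis is valid for what it measures, but it mixes residual with new lesions. A significant result therefore shows fewer lesions present, not fewer lesions arising. With no preventive effect, clearance alone could move the difference from about +4.0 to +5.5 (cryosurgery at 67%) through zero (89%) to −1.1 to −1.5 (97%). These figures rest on 89% DL-PDT clearance, constant clearance per session, equal new-lesion rates, and assumed baseline counts and rates that the document does not give. They show that the sum can mislead about prevention in either direction; they do not predict that it will. Alpha and the stated 26 and 29 per group are not affected.

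**What to change.** Keep the sum as the primary endpoint. Before database lock and before any look at data by arm:

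- Name one key secondary endpoint: the cumulative number of new AK lesions at visits 2 to 6, each counted once, when it first appears at a position not mapped at an earlier visit. Lesions at mapped positions count as persistent or recurrent.
- Test it in fixed sequence at two-sided 0.05, only after a significant primary. Report its estimate and 95% confidence interval whatever the primary shows.
- State that a significant primary alone supports a claim of fewer AK lesions present, and that a confirmatory claim of prophylaxis requires the key secondary to succeed.

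The cost is wording in the protocol and analysis plan. The fixed sequence uses no extra alpha, and no new assessment is needed: lesions are already charted and marked on plastic sheets, "ensuring that the lesions will be found again at the next visit".

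There are three downsides. A prophylaxis claim needs a second significant result. The power of that test is unknown, because the document gives no mean or SD for new lesions. If the primary fails, for example because cryosurgery clears better, prevention stays descriptive; the sequence does not rescue that case.

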### Quality assurance

Study monitoring is conducted by experienced monitors. Monitoring is based on an a priori developed monitoring plan that includes inspecting the completeness of documentation and comparing the documentation with the source data.

Source data verification (SDV) is carried out at regular intervals. In all patients, the following data are compared with the source data: Basic patient documentation (sex and date of birth), inclusion and exclusion criteria, localization of AK study lesions, dates of all study visits, primary endpoint, adverse events, and the reason for premature study termination, if applicable.

### Data management and archiving

The patient identification list is controlled by the Investigator/Principal Investigator and will not be forwarded to other parties. Data recorded by pCRF will be pseudonymized. The responsible data manager monitors compliance to data security and protection rules according to Standard Operating Procedures (SOPs) and Working Instructions (WI).

All data management activities are conducted within a consistent, auditable, and integrated electronical environment (data security, data entry, and data validation). The responsible data manager takes care that no unauthorized access to the computer system takes place. By conducting adequate data backup procedures, the data manager makes sure that no data will be lost. Only specified persons involved in the trial and sworn to secrecy get authorization to enter or access the data trail of all transactions. Range, validity, and consistency checks are implemented into the system for application during data entry. After the first verification of the CRFs, all data collected on the CRFs are entered into the study database. Data entries as well as data modifications and data corrections are routinely recorded via the audit trail. In the case of necessary corrections or existing data inconsistencies, data queries are consecutively generated by the data manager. Queries are sent to the Principal Investigator/Investigator. Afterwards, data in the database are corrected according to the answered and resolved queries. After the database lock, data are imported into standard statistical software systems and forwarded to the biometrician in charge.

Archiving of the clinical database including the audit trail is conducted by the responsible data manager in a machine-independent format. The originals of all essential trial documents are filed in the TMF that will be stored at the archive of the Center for Clinical Studies Regensburg (ZKS) for at least 15 years after preparation of the final report. The investigators files all site-specific documents (e.g. correspondence with ethic committee), the patient identification list, the signed informed consent forms, copies of the pCRFs, and general trial documents (e.g. protocol, amendments) in the ISF, which will be also archived for at least 15 years at the individual trial sites.

